## Abstract

**Background:**

Many older persons use the thyroid hormone levothyroxine which is often continued for life. Scientifically, there is much uncertainty whether simple continuation is the optimal approach. First, the physical need for levothyroxine can decrease with age thereby posing a higher risk of overtreatment and adverse effects. Second, large trials in subclinical hypothyroidism have shown no benefit for the use of levothyroxine. Interestingly, guidelines do not address re-evaluation of the indication. This self-controlled trial aims to determine the effects of discontinuation of levothyroxine treatment in older adults.

**Methods and analysis:**

Participants are community-dwelling subjects aged ≥60 years using levothyroxine continuously at a stable dosage of ≤150 µg and a level of thyroid-stimulating hormone (TSH) <10 mU/L. After a control period of 12 weeks, levothyroxine treatment is discontinued gradually using a stepwise approach with regular monitoring of thyroid function guided by their GP. The primary outcome is the proportion of participants withdrawn from levothyroxine while maintaining a free T4 level within the reference range and a TSH level <10 mU/L, 52 weeks after the start of discontinuation. Secondary outcomes are compared with the control period (self-controlled) and include among others, the effects on thyroid-specific and general health-related quality of life. Furthermore, patients’ attitudes towards deprescribing and regret regarding discontinuing levothyroxine treatment will be recorded. A total of 513 participants will be recruited to estimate the expected proportion of 50% with a 95% CI ranging from 45% to 55%.

**Ethics and dissemination:**

Approval was obtained from the institutional Medical Ethics Committee. The Older People Advisory Board Health and Well-being has reviewed the research proposal and their comments were used for improvement. In line with the funding policies of the grant organisation funding this study, the study results will be proactively disseminated to the general public and key public health stakeholders.

**Trial registration number:**

NL7978; NCT05821881.

Strengths and limitations of this studyThis is a self-controlled trial to assess the effect of discontinuation of levothyroxine treatment specifically in older adults (aged ≥60 years), using both thyroid function and thyroid-related quality of life as outcome parameters.Stepwise dose reduction with regular measurements of thyroid function reduces the risk of prolonged periods of undertreatment potentially resulting in symptoms of hypothyroidism.The primary endpoint, successful withdrawal of levothyroxine, is a biochemically defined endpoint, which is not affected by the unblinded design of the study.The unblinded design of this study may introduce performance bias and detection bias in the outcomes of the secondary endpoints.

## Introduction

Levothyroxine is one of the most widely prescribed drugs and is currently ranked in the top 3 of total prescriptions in the USA and UK.^1 2^ It is most frequently prescribed and initiated in older adults (aged 50–70 years).^3^ Notably, levothyroxine prescriptions have increased substantially, from 2.3% to 3.5% over the past decades despite a low prevalence (0.1%–1.9%) and a stable incidence of overt hypothyroidism.^2 4^ A contributing factor to the rise in levothyroxine prescriptions is likely an increase in the treatment of subclinical hypothyroidism.^5^ Subclinical hypothyroidism is a common condition defined by an elevated level of thyroid-stimulating hormone (TSH) and a free T4 (fT4) level within the normal reference range. The prevalence of subclinical hypothyroidism increases with age (5%–20% in men and women older than 60 years).^6^ A recent US study showed that most individuals who started on levothyroxine were diagnosed with subclinical hypothyroidism (65.7%).^7^ Furthermore, studies indicate that TSH levels at the initiation of treatment are falling,^8 9^ which is worrisome because it may increase the chance of ineffective treatment.^10^ This holds especially for older adults with subclinical hypothyroidism with TSH levels <10 mU/L since recent randomised clinical trials show that levothyroxine treatment does not improve thyroid-related symptoms, quality of life, depressive symptoms or cognitive function in older people.^11–13^

Treatment with levothyroxine for both overt and subclinical hypothyroidism, is often continued for life, as current guidelines do not advise re-evaluation of the indication and effect.^8 14^ Initial indications for treatment are not always well documented and can be inaccurate or even inappropriate.^15^ Patients may have started levothyroxine in the past for a diagnosis made during transient hypothyroidism.^15–17^ Furthermore, thyroid (dys-)function varies over time,^18^ and thyroid metabolism changes with age.^19^ Therefore, it is likely that a considerable proportion of older adults are treated with levothyroxine without a clear indication according to current guidelines. This could be harmful, considering that oversuppression (TSH <0.45 mU/L) has been reported in 41% of older levothyroxine users^20^ and increases the risk of bone fractures and atrial fibrillation.^21 22^ The risk of oversuppression increases with treatment duration^8^ and although guidelines warrant careful medication monitoring, levothyroxine dosages may remain unchanged for a long time.^23^

Taking into account the high levothyroxine use in older age, the controversy regarding treatment of subclinical hypothyroidism, the lack of re-evaluation of indications, and the health risks associated with oversuppression, it can be hypothesised that discontinuation of levothyroxine treatment can be achieved without negative consequences for a considerable proportion of older adults. A meta-analysis based on observational studies including participants aged 2–81 years suggested that approximately 37% remain euthyroid after thyroid hormone discontinuation.^24^ However, the evidence was of low quality, the adult participants were mostly middle-aged, and no study followed a systematic approach for deprescribing levothyroxine.

Therefore, the primary aim of this self-controlled trial is to investigate what proportion of community-dwelling levothyroxine users aged 60 years and older can withdraw from levothyroxine treatment successfully. Secondary aims are as follows: (1) to study what proportion of participants can achieve a substantial dose reduction of levothyroxine at 52 weeks (a) defined as ≥50% and (b) defined by the participants themselves; (2) to study the effect of discontinuation of levothyroxine treatment at 52 weeks on (a) thyroid-related quality of life and (b) general health; (3) to determine how participants reflect on their decision to discontinue levothyroxine treatment.

## Methods

### Study design

This is a self-controlled trial investigating the stepwise discontinuation of levothyroxine treatment in adults aged 60 years and older with a follow-up of 1 year. Outcomes will be measured 12 weeks before the start of discontinuation, at the start of discontinuation, at 6 weeks, at the end of discontinuation and after 52 weeks. The outcomes will be compared within participants. In this way, the research questions can be studied validly in a self-controlled design, without the need for an extra control group. The formal role of a control group in a randomised trial is to estimate what would have happened in the experimental arm in the absence of the intervention.^25^ This effect is immediately clear in our study: levothyroxine treatment is simply continued in almost all patients. Therefore, a control group in our study will only reveal information that is already known.^26^ The primary outcome of the study is based on a biochemically defined thyroid function status, an fT4 level within the reference range and a TSH level <10 mU/L. Since this biochemically defined outcome is independent of participants’ views or experiences, is not influenced by personal interpretation and is therefore not affected by an unblinded design, we considered a control group as not required. A TSH level of <10 mU/L was based on the results from the recently published randomised clinical trials on levothyroxine treatment in older adults with subclinical hypothyroidism.^11–13^

### Study setting

Community-dwelling participants are recruited from general practitioner (GP) practices in the Netherlands. Participating GPs identify eligible patients for whom they are the primary caregiver concerning levothyroxine treatment, from electronic medical records using the inclusion and exclusion criteria mentioned below. GPs may exclude patients when they feel study participation could harm their patient. Reasons for exclusion are collected. Selected patients receive an invitation to participate in the study and an information leaflet from their GP (see online supplemental appendix 1). Written informed consent is obtained from all patients who are willing to participate in the study (see online supplemental appendix 1). Participants are enrolled by the study centre.

10.1136/bmjopen-2022-070741.supp1Supplementary data

### Study population

A participant must meet all of the following inclusion criteria:

Age ≥60 yearsUsing any levothyroxine monotherapy medicament (ATC: H03AA01) at a stable dosage for ≥1 year.

Exclusion criteria are as follows:

Last measurement of TSH ≥10 mU/L during levothyroxine treatment.The dose of treatment is >150 mcg levothyroxine per day (for safety reasons).The current reason for levothyroxine treatment: patients with a history of thyroidectomy; radioactive iodine treatment or neck irradiation; congenital hypothyroidism; secondary hypothyroidism or concurrent amiodarone or lithium use.Concurrent treatment with liothyronine (the synthetic form of thyroid hormone T3), thiamazole, carbimazole or propylthiouracil (inhibitors of T3 and T4 synthesis).Diagnosis of heart failure NYHA (New York Heart Association) grade IV.Participation in ongoing trials of therapeutic interventions.Life-expectancy<6 months.Diagnosis of dementia.Incapacitated adults.Persons planning to move out of the region in which the study is being conducted in the next months.

### Study phases and interventions

This study consists of three phases: a control phase of 12 weeks (T-12 to T0), the discontinuation phase (minimum of 6 weeks, maximum of 36 weeks; T0 to Tx) and a follow-up phase (from the end of discontinuation till 52 weeks after the start of discontinuation; Tx to T52) (see figure 1).

**Figure 1 F1:**
[figure not shown]
Flow of participants.

#### Control phase

Participants enter the study during a control period with prebaseline measurements of thyroid function and secondary outcome parameters to determine natural variation after which treatment with levothyroxine is continued per usual care for at least 12 weeks (see table 1). Participants with a prebaseline TSH level ≥10 mU/L do not proceed to the discontinuation phase (exclusion). When a participant presents with a suppressed TSH (indicative of oversuppletion with levothyroxine), the discontinuation phase can be started immediately. Participants are requested to complete their questionnaires prior to thyroid function assessment, so the results do not influence their answers. Furthermore, they are instructed to schedule all laboratory visits at the same time preferably in the morning before ingesting levothyroxine and consumption of food and/or drinks.

**Table 1 T1:** Schedule of measurements

		Study phase				
	Control phase	Discontinuation phase				Follow-up phase
		Start of step 1	Control of step 1	Control of steps 2–5	Control of last step‡	
**Time (weeks**)	−**12**	**0**	**6**	**12, 18, 24, 30**	**6/12/18/24/30/36**	**52**
Primary outcome						
TSH, fT4	X	X	X	X†	X	X
Secondary outcomes						
ThyPRO-39	X	X	X		X	X
TSQM	X	X				
EQ5D VAS	X	X	X		X	X
DRS						X
GAS*						X
Descriptives						
Demographics and clinical characteristics	X					
ISCOPE	X					X
rPATD	X	X				
GAS*	X					

*Substantial dose reduction of levothyroxine.

†If applicable.

‡End of the discontinuation phase.

DRS, Decision Regret Scale; EQ5D, EuroQol 5 Dimensions; fT4, free T4; GAS, Goal Attainment Scale; ISCOPE, Integrated Systematic Care for Older Persons; rPATD, revised Patients’ Attitudes Towards Deprescribing; ThyPRO, Thyroid-Related Quality of Life Patient-Reported Outcome; TSH, thyroid stimulating hormone; TSQM, Treatment Satisfaction Questionnaire for Medication; VAS, Visual Analogue Scale.

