#### Discontinuation phase

The discontinuation phase starts with baseline measurements of thyroid function and secondary outcome parameters (see table 1), followed by a consultation of the participant with their GP during which discontinuation of levothyroxine is initiated, except when TSH level ≥10 mU/L. Levothyroxine is discontinued stepwise, and at intervals of ≥6 weeks to ascertain a steady-state concentration has been reached before the following control visit. This is in line with standard clinical practice. During each ‘6 week’ visit, the GP evaluates thyroid function and symptoms with the participant. On agreement, the daily dose of levothyroxine can then be lowered provided thyroid function is within the predefined limits, that is, a normal fT4 and TSH <10 mU/L. With each step, the dose of levothyroxine is reduced by approximately 25 mcg (the use of whole tablets is preferred) until a daily dose of 25 mcg or less is reached. The GP is free to adjust the size of the dose reduction if necessary. The maximum dose reduction in medication is 50 mcg in the first step. In the final step, the medication is discontinued completely if the laboratory results are still within the predefined limits. The discontinuation phase ends after the evaluation of complete withdrawal of the levothyroxine treatment (ie, 6 weeks after the final discontinuation step). Secondary outcome parameters are collected at the first ‘6 week’ visit and the end of discontinuation (see table 1).

Participants are requested to stop the discontinuation phase when a TSH level ≥10 mU/L or an fT4 level below the normal range is identified during a control visit and is confirmed by an extra thyroid function measurement within 2 weeks. When the extra measurement does not confirm a TSH level ≥10 mU/L or a low fT4 level, the participant is allowed to proceed with the discontinuation phase. Factors other than thyroid function, such as symptoms, may however be a reason to prematurely stop the discontinuation or restart levothyroxine. On stopping the discontinuation phase, it is at the discretion of the physician and the participant to decide whether the dose of levothyroxine at that moment will be maintained or increased. Participants who have stopped the discontinuation phase prematurely will be followed up in accordance with the protocol if possible.

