### Sample size calculation

The sample size calculation is based on the primary outcome, the proportion of participants successfully stopping levothyroxine treatment between baseline and final follow-up at 52 weeks. Since population proportions of successful levothyroxine treatment cessation are unknown (the aim of this study), we estimated a proportion of 50% of the participants who successfully discontinue levothyroxine treatment. An estimated proportion of 50% results in the most conservative estimate (resulting in the highest calculated sample size) and is in line with the limited available evidence.^37–39^ We have chosen a sample size of 385 participants because this allows us to estimate the expected proportion of 50% with a 95% CI of which the lower and upper limit is expected to deviate by 5 percentage points from the found percentage (ie, 45% to 55% when the found percentage is indeed 50%).

Taking a maximum of 25% loss to follow-up into account over the duration of 15 months (exclusion at T-12 when TSH level ≥10 mU/L and/or fT4 below reference range, withdrawal, moving away or death between T-12 and T52) a maximum of 513 participants will be recruited. Based on a data query from the academic network of general practices in the region of Leiden, it was estimated that the projected sample size will be reached after inclusion of 53 standard general practices.

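### The start rule ignores a low free T4 at week 0, and the week −12 exclusion is stated in two different ways

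*Protocol article*

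**What the plan says.** All references are to the protocol article.

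- **Week −12, Control phase:** "Participants with a prebaseline TSH level ≥10 mU/L do not proceed to the discontinuation phase (exclusion". fT4 is not mentioned.
- **Week −12, Sample size calculation:** the 25% loss allowance includes "exclusion at T-12 when TSH level ≥10 mU/L and/or fT4 below reference range".
- **Week 0, Discontinuation phase:** after baseline measurements and a GP consultation, "discontinuation of levothyroxine is initiated, except when TSH level ≥10 mU/L". fT4 is again not mentioned.
- **Each later reduction, Discontinuation phase:** at the six-weekly visits the dose may be lowered "provided thyroid function is within the predefined limits, that is, a normal fT4 and TSH <10 mU/L".
- **Complete withdrawal, same section:** "In the final step, the medication is discontinued completely if the laboratory results are still within the predefined limits".
- **Step size, same section:** "With each step, the dose of levothyroxine is reduced by approximately 25 mcg", and "The maximum dose reduction in medication is 50 mcg in the first step".
- **Stop rule, same section:** TSH ≥10 mU/L or a low fT4 ends the taper if found at a control visit and if it "is confirmed by an extra thyroid function measurement within 2 weeks".

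Table 1 schedules TSH and fT4 at both week −12 and week 0.

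**The concern.** There are two problems.

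**Consistency.** Someone with low fT4 and TSH below 10 mU/L at week −12 is excluded according to the Sample size calculation section. Under the Control phase section the same person can go on to week 0, and so into the population that the Data analysis plan section builds from those enrolled at baseline. Two sites following different sections would treat that person differently.

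**Safety.** From week 6 onwards the protocol regards a low fT4 as a reason not to reduce further, and a confirmed low fT4 as a reason to stop. At week 0 the same result is available, but the start rule does not use it. A participant already below range on the current dose could therefore be given less, with no biochemical rule acting until the next control visit. This runs against the aim, stated under (Serious) adverse events, of avoiding prolonged under-replacement.

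**Working it through.** **The rules side by side**

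| Decision | Section | TSH limit | fT4 limit |
|---|---|---|---|
| Exclude at week −12 | Control phase | ≥10 mU/L | none stated |
| Exclude at week −12 | Sample size calculation | ≥10 mU/L | below range |
| Withhold first reduction at week 0 | Discontinuation phase | ≥10 mU/L | none stated |
| Withhold a later reduction | Discontinuation phase | ≥10 mU/L | not normal |
| Withhold complete withdrawal | Discontinuation phase | ≥10 mU/L | not normal |
| Stop the taper at a control visit | Discontinuation phase | ≥10 mU/L, confirmed | below range, confirmed |

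The Study population section does not settle the matter, because its thyroid-function criterion is also TSH only. The stop rule does not reach back to week 0: Table 1 labels week 0 as the start of step 1 and week 6 as its control, so week 0 is not a control visit.

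**Who is exposed.** The taper runs down to 25 mcg or less, after which the final step needs results within limits. A participant already on 25 mcg or less is therefore protected, because the first step is also the final one. The same holds for stopping 50 mcg in one step. The gap concerns participants on more than 25 mcg whose first reduction leaves some dose.

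**Size of the first reduction**

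- Usual 25 mcg step: 25/150 = 17% of the daily dose at 150 mcg; 25/50 = 50% at 50 mcg.
- Maximum 50 mcg step that still leaves 25 mcg or more: 50/150 = 33% at 150 mcg; 50/75 = 67% at 75 mcg.

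**Time before the biochemical rule acts.** With the minimum 6-week interval and 0 to 2 weeks for confirmation: 6 + 0 to 2 = 6 to 8 weeks on the lower dose.

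**The plan's own sample size.** Inputs from the Sample size calculation section are p = 0.50, half-width 0.05 and 25% loss.

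- n = 1.96² × 0.25 / 0.05² = 384.2, rounded up to 385, as stated.
- 385 / 0.75 = 513.3, given as 513.
- Allowance: 513 − 385 = 128.

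**Effect of closing the gap.** The article gives no rate of low fT4 with TSH below 10 mU/L at week 0, so I assume 0.5% to 2%. The number reaching week 0 lies somewhere between 385 and 513.

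- Of 385: 0.005 × 385 = 1.9 and 0.02 × 385 = 7.7, so about 2 to 8 people.
- Of 513: 0.005 × 513 = 2.6 and 0.02 × 513 = 10.3, so about 3 to 10 people.

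As a worst case, suppose the 128 are all used up and every non-starter also leaves the analysis. The half-width is 1.96 × √(0.25/n):

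| n analysed | Half-width (percentage points) |
|---|---|
| 385 | 4.99 |
| 383 | 5.01 |
| 377 | 5.05 |
| 375 (385 − 10) | 5.06 |

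**The case against.** The strongest reply is that the two week −12 statements can be applied together. The Control phase section gives one sufficient reason for exclusion and does not say it is the only one; the Sample size calculation section adds a second. On that reading low fT4 is already excluded at week −12. What remains is a participant whose fT4 was in range at week −12 and low 12 weeks later, on a dose stable for at least a year, with TSH still below 10 mU/L. That should be uncommon. The first step also follows a GP consultation, the GP may alter the step size, symptoms can end the taper, and fT4 is rechecked at week 6. The flow figure and the full protocol are not shown and may state the rule correctly.

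Much of this stands as a limit on size. The superset reading narrows the week −12 problem to unclear wording. It does not help at week 0, where the text sets an explicit exception that names TSH only. The safeguards are discretionary and could differ across the planned 53 practices. A correct rule in the figure would not remove the mismatch in the text.

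It is also fair to say that the percentage dose cuts describe ordinary tapering. They show what an affected participant would receive; they do not measure harm. Finally, a single low fT4 would bar the start, whereas at a control visit it must be confirmed before the taper ends. The remedy therefore equalises the limits but not the confirmation procedure.

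**Conclusion.** The concern holds on the text. The week −12 exclusion is stated inconsistently, and the week 0 rule, followed as written, lets a participant on more than 25 mcg with low fT4 and TSH below 10 mU/L take a first reduction. If the Sample size calculation wording governs week −12, the gap shrinks to a low fT4 first seen at week 0.

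The number affected is unknown and probably small: about 2 to 10 people if 0.5% to 2% of those reaching week 0 are affected, a range that is an assumption and not taken from the article. Each would spend 6 to 8 weeks on a reduced dose before the biochemical stop rule could act, at the minimum visit interval. No bias in the primary proportion is claimed, complete withdrawal in one step is not affected, and the sample size is sound. It should be fixed because it is a safety rule that contradicts the protocol's own later limits and costs almost nothing to correct.

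**What to change.** In the Control phase and Discontinuation phase sections, state that discontinuation is not started when TSH is ≥10 mU/L or fT4 is below the reference range. This matches the Sample size calculation section and gives the first reduction the same TSH limit and lower fT4 limit as every later one. Leave the single-measurement TSH exclusion as it is and add no confirmation step.

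The cost is one clause in each of two sections and a note to the study centre and participating GPs. No extra blood test is needed, because fT4 is already taken at both visits. A few more participants may not start at week 0. The 25% allowance lists week −12 exclusions but does not explicitly list week 0 non-starters; even in the worst case above the half-width stays within 0.1 percentage points of the 5-point target, so 385 and 513 need not change.
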